##### Subgroup analyses

The following a priori defined subgroups will be investigated: sex (male/female), migraine with aura (yes/no) and baseline frequency of migraine days (medium = 5–9 days/4 weeks; high = 10–14 days/4 weeks). For each subgroup, the main effect of the subgroup and the interaction term “subgroup × treatment” will be added to the already described statistical model. In the case of a trend (*p* < 0.10) for an interaction effect—indicating a difference in the treatment effect between the subgroups—separate models will be fit for each subgroup.

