##### Visit 2 (baseline visit, just prior to 12-week intervention)

Before starting the intervention, the study patient must meet all of the following inclusion criteria.

The patient:continues to meet all baseline (Visit 1) eligibility criteria;has experienced between 5 and 14 migraine days; andhas demonstrated compliance with the headache diary during the run-in period.

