#### Fixed sample size estimation

##### Assumptions

Sample size estimation is based on the following assumptions:We expect the baseline number of migraine days per 4 weeks to be 10 days in our patient population.Placebo effect: based on recent findings [64], we assume a rather strong placebo effect of 32% reduction in the primary endpoint. This corresponds to an absolute reduction of 3 migraine days per 4 weeks.IMP effect: synthesising previous findings [4, 64] and our pilot data [65], we aim to detect a difference of 2 days between placebo and IMP.We assumed the absolute reduction in migraine days to be normally distributed with a standard deviation of 3 days.We assume a conservative intra-patient correlation between IMP and placebo of 0.4.Drop out: a high drop-out rate of 30% is assumed.

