##### Re-sampling

The sample size was estimated using a re-sampling method. Each sample size (n_i_ = 1,...,49 = 12, ..., 60) was evaluated by sampling *R* = 999 times the reduction in migraine days from a bivariate normal distribution as already described. For each sample, whether superiority of the IMP over placebo could be shown (i.e. whether a two-sided paired *t* test resulted in significant *p* < 0.05) was tested.

In order to show the superiority of the IMP over placebo with a statistical power of 90%, 45 patients should be recruited in total to ensure 31 evaluable patients, assuming a drop-out rate of 30%. Figure 3 shows how the sample size depends on the expected reduction in number of migraine days in the IMP arm.

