##### Primary analysis

The primary endpoint, the number of migraine days in the last 4 weeks of treatment, will be measured twice for each patient, once after the placebo treatment period and once after the IMP treatment period. The number of migraine days in the 4 weeks before start of treatment will be assessed for both treatment periods, thus there will be two baseline values that will be used as covariates. This process has the aim of correcting for any potential seasonal variation in baseline migraine frequency or carry-over effects.

The primary analysis will be performed using a linear, mixed-effects regression model. The primary model will include the primary endpoint (the number of migraine days in the last 4 weeks of treatment) as the response variable, the respective baseline value as a covariate, treatment (IMP vs placebo) and period (first vs second) as main effects, the two interaction terms “treatment × period” and “treatment × baseline value”, and patient as random effects. A significant interaction term between treatment and period would indicate a carry-over effect. Since it is not known how strongly the primary endpoint correlates with the baseline value, it is not known whether including the baselines as covariates in the model is sensible. Therefore, the already described primary model will be compared to models without the interaction term “treatment × baseline value” and without both the interaction term “treatment × baseline value” and the baseline value as a covariate by means of Akaike’s Information Criterion (AIC).

The primary analysis will be done on the ITT set.

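### For the baseline-frequency subgroup, subgroup × treatment is added on top of treatment × baseline value, so it tests a step at 9/10 days and not the medium-versus-high difference

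*Protocol article*

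**What the plan says.** The Primary analysis section specifies a linear mixed model for migraine days in the last 4 weeks of treatment. It has the period's own baseline count as covariate, treatment, period, a patient random effect and "the two interaction terms “treatment × period” and “treatment × baseline value". This model is compared by AIC with a version lacking treatment × baseline value, and with one lacking both that term and the baseline.

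The Subgroup analyses section names three a priori subgroups: sex, aura and "baseline frequency of migraine days (medium = 5–9 days/4 weeks; high = 10–14 days/4 weeks". For each of them, "the main effect of the subgroup and the interaction term “subgroup × treatment” will be added to the already described statistical model". No exception is made for the frequency subgroup. An interaction with p<0.10 is read as showing that the treatment effect differs between subgroups, and it triggers separate models per subgroup.

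The frequency bands match the entry condition at Visit 2, that the patient "has experienced between 5 and 14 migraine days" in the run-in.

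**The concern.** The medium/high indicator is the baseline covariate cut in two. Sex and aura bring new information into the model. This indicator brings in a coarse copy of a variable whose interaction with treatment is already there.

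With both interactions present, treatment × baseline value absorbs any linear change of benefit with frequency. What is left for subgroup × treatment is a sudden change between 9 and 10 days. The model and the interpretation given to it then do not match: a non-significant term would be taken as similar benefit in medium- and high-frequency patients, even when benefit differs between them because it changes steadily with frequency. The decision to fit separate models rests on this term.

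**Working it through.** **The plan's own figure.** Inputs from the sample size section: "we aim to detect a difference of 2 days between placebo and IMP", reductions "normally distributed with a standard deviation of 3 days", within-patient correlation 0.4, drop-out 30%, and the criterion "whether a two-sided paired *t* test resulted in significant *p* < 0.05".

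- SD of the paired difference = 3 × √(2 × (1 − 0.4)) = 3.286 days.
- Exact paired-t power: 0.896 at n = 30 and 0.906 at n = 31, so 31 evaluable patients are needed.
- 31 / 0.7 = 44.3, rounded up to 45.

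This reproduces the statement "with a statistical power of 90%, 45 patients should be recruited in total to ensure 31 evaluable patients". The plan gives no power for the subgroup test.

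**Overlap of the cut and the count.** Assume first baselines spread evenly over 5, …, 14 (not in the document).

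- Mean of the medium band is 7 and of the high band 12, a difference of 5 days.
- Covariance of indicator and count = 0.25 × 5 = 1.25. SDs are 0.5 and √8.25 = 2.87.
- Correlation = 1.25 / (0.5 × 2.87) = 0.87. Variance inflation = 1 / (1 − 0.87²) ≈ 4.1, so the SE rises by √4.1 ≈ 2.0 when the two baselines of a patient are equal.

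**Hand check at n = 31, equal baselines.**

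- SE of the subgroup × treatment estimate without treatment × baseline value ≈ 3.286 / √(31 × 0.25) = 1.18 days.
- With it, ≈ 1.18 × 2.03 = 2.4 days.
- If benefit changes linearly by 0.4 day per baseline day, the true subgroup difference is 0.4 × 5 = 2 days. The expected step coefficient is 2 without the competing term and 0 with it, so with it the test rejects at its nominal 10%.

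**Simulation.** AB/BA crossover, random patient intercept, REML, SD 3, correlation 0.4, mean effect 2 days, 31 complete patients, 600 runs per case. The subgroup is fixed by the first baseline, and the two baselines correlate 1, 0.8 or 0.5 (assumed). Percentages are the share of trials in which subgroup × treatment has p<0.10.

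| True pattern (nominal subgroup difference) | Baseline correlation | With treatment × baseline | Without it |
|---|---|---|---|
| Linear, 2 days | 1 / 0.8 / 0.5 | 10 / 12 / 9% | 50 / 44 / 32% |
| Linear, 4 days | 1 / 0.8 / 0.5 | 10 / 10 / 10% | 92 / 84 / 71% |
| Step at 10 days, 2 days | 1 / 0.8 / 0.5 | 21 / 26 / 33% | 49 / 49 / 48% |
| Step at 10 days, 4 days | 1 / 0.8 / 0.5 | 48 / 60 / 72% | 93 / 94 / 93% |

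The SE is 2.5, 2.1 and 1.8 days with the term, against about 1.2 without it. In the 4-day linear case with equal baselines the mean coefficient is 0.03 with the term and −4.03 without.

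Two further simulations, with period-specific baselines and variances treated as known, gave 10% and 13% with the term against 49% and 50% without, for the 2-day linear case. With 45 patients the pattern is the same: 9–12% with the term and 38–98% without, over the linear cases.

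**AIC.** When the AIC-chosen model is used, treatment × baseline value is kept in 64–70% of runs for the 2-day linear case and 98–99% for the 4-day case. The rejection rate stays at about 9–10%.

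**The case against.** **The test still works for a step.** A reader might infer that the subgroup test can never show a difference. That is too strong. If benefit changes abruptly at the cut, the coefficient is unbiased and only power is lost, as the last two rows of the table show.

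**The trend is estimated elsewhere.** A reader might also infer that the trial would report no difference even if benefit rose steeply with frequency. The documents do not support this, because treatment × baseline value is itself in the primary model. At 0.4 day per baseline day that term reaches p<0.10 in about 54–62% of simulated trials, as good as the corrected subgroup test. What fails is the reading of the subgroup term and the gate that hangs on it.

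**AIC may drop the competing term.** If it does and the reduced model is used, the overlap with treatment × baseline value disappears. But AIC tends to keep the term when baseline does modify the effect, so this is little protection.

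**The overlap is partial.** The covariate is period-specific. If the subgroup is fixed at the first baseline, the SE rises less than twofold, about 1.7-fold at a baseline correlation of 0.8. This stands, yet rejection under a linear pattern remains near 10%.

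**The second baseline.** A reader might infer that patients could change group, or fall outside 5–14, at the second run-in. That needs the subgroup to be redefined in each period. The period-specific wording describes the covariate. The subgroups are called a priori and their bands match the Visit 2 entry range, so one classification per patient is the natural reading.

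**The Discussion.** It mentions benefit in moderately to strongly affected patients or at least a subgroup of them. It does not single out frequency or say that benefit is confined to a subgroup, so it adds no weight here.

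**The SAP may settle it.** It may, but this is not an omitted detail: the article states which model the terms are added to.

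**Conclusion.** The point holds for one of the three subgroup analyses. As written, the frequency subgroup's interaction does not estimate the medium-versus-high difference that the plan says it indicates. A smooth 2-day difference would pass the p<0.10 gate in about 9–13% of trials instead of about 32–50%, and a 4-day step in about 48–72% instead of about 93%.

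These figures rest on assumptions that the document does not give: even spread of baselines over 5–14, baseline correlations of 0.5 to 1, and a linear or single-step pattern. That the term measures a departure from linearity follows from the model itself and does not depend on them. Even after correction, power for a 2-day difference is at most about 50% with 31 patients, so a null result would still be weak evidence of equal benefit.

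**What to change.** In Subgroup analyses, add one sentence: for the baseline-frequency subgroup only, subgroup × treatment replaces treatment × baseline value, the baseline main effect is kept, and each patient is classified once from the migraine-day count of the first run-in.

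An alternative is to use the continuous treatment × baseline interaction as the test and report the estimated effects for 5–9 and 10–14 days. This is a different test, of a slope and not of a two-group contrast, so one of the two should be chosen in advance.

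The cost is one sentence in the protocol or SAP before database closure. It needs no new data and no change to the sample size or the primary analysis.

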##### Secondary analysis

The secondary (exploratory) objectives are to assess the therapeutic efficacy of externally induced mild ketosis by the IMP regarding the following secondary endpoints:change in number of headache days of any severity from baseline (meeting ICHD-3 criteria) during the last 4 weeks of intervention;change in number of headache days of any severity from baseline (meeting ICHD-3 criteria) during the last 4 weeks of follow-up;change in consumption of acute migraine medication from baseline (analgesics or triptans)— measured in days with acute headache medication use—during the last 4 weeks of intervention;change in average migraine intensity from baseline—assessed with a VAS from 0 to 10 for each migraine episode—during the last of 4 weeks of the intervention period; andchange in disability from baseline—assessed with the Migraine Disability Assessment (MIDAS) and the Headache Impact Test (HIT-6)—to the last of 4 weeks of the intervention period.

All of these secondary endpoints will be analysed as described for the primary endpoint with the corresponding baseline measure as covariate, if available.

All secondary analyses are done on the ITT set.

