## Discussion

We propose a single-centre, randomised, double-blind, placebo-controlled, crossover trial to determine whether treatment with βHB in mineral salt form has a positive effect on migraine frequency and associated symptoms. To our knowledge this is the first RCT using exogenous KB salts worldwide. If proven effective, βHB might offer a new prophylactic treatment option for moderately to strongly affected migraine patients, or at least a subgroup thereof. A demonstration of its safety might additionally pave the way for clinical trials assessing its use in related diseases.

Planning clinical trials in migraine is challenging for the following reasons: migraine is an episodic disease with a fluctuating nature (i.e. in some patients, migraine frequency can vary substantially from one month to the next or one season to the other, which makes it harder to demonstrate a treatment-related effect); the placebo effect is quite large, between 20 and 40% [67], which further adds to this problem; individual migraine attacks are of different length, and in more severely affected patients are sometimes hard to identify [68]; some patients suffer from headache of a different quality in addition to migraine and this distinction must be made by the patient subjectively [68]; and there is no objective biomarker for migraine or disease severity [68].

In order to address these problems, we have: incorporated two baseline periods to account for seasonal changes, and chosen a conservative effect size as well as a study population of moderate to high-frequency episodic migraineurs (5–14 headache days per month), in order to make it easier to demonstrate a sufficiently large effect size within a short timeframe, without introducing any confounds associated with chronic migraine, such as frequent co-morbidities [69]; calculated with a quite large placebo effect of 30%; chosen migraine days versus migraine attack frequency as the primary outcome; included a thorough briefing of each patient on the characteristic features of a migraine versus a headache attack; and included a detailed medical history and diagnostic consultation by a neurologist, as well as a carefully constructed headache diary.

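### Any of three subgroup interactions at p<0.10 is read as a real difference and alone triggers separate subgroup models: a cheap improvement of minor severity

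*Protocol article*

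**What the plan says.** Subgroup analyses names three factors in advance: "The following a priori defined subgroups will be investigated: sex (male/female), migraine with aura (yes/no) and baseline frequency of migraine days". For each factor, "the main effect of the subgroup and the interaction term “subgroup × treatment” will be added to the already described statistical model". That model is the mixed model of the Primary analysis section, with the baseline value, treatment, period, treatment × period, treatment × baseline and a random patient effect.

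The section then fixes a reading and an action. An interaction at p<0.10, which it calls a trend, is taken as "indicating a difference in the treatment effect between the subgroups", and on that signal "separate models will be fit for each subgroup". If the threshold is not met, no subgroup-specific models are planned. The section gives no significance level for the separate models and does not say what may be concluded from them.

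The only significance level that the article states for a treatment comparison is in the sample size section (Re-sampling): "whether a two-sided paired *t* test resulted in significant *p* < 0.05".

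**The concern.** Two parts of this written rule are weak.

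The first is the reading. One interaction at p<0.10 among three is weak evidence that the treatment effect differs between subgroups. Such a result is common when the effect is the same in everyone.

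The second is the action. The separate models are fitted only when the observed difference between subgroups is large, so the effects reported from them are selected and tend to be exaggerated. They also divide a trial of 31 evaluable patients into small cells. There, a non-significant result in one cell is likely even if the planned benefit is present in both. The natural reading of the output, that the product works in one subgroup and not in the other, is then often wrong.

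What is at stake is the description of who benefits. The primary result is not at stake.

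**Working it through.** **Inputs from the protocol article.** Fixed sample size estimation gives a difference of 2 days, an SD of 3 days, an intra-patient correlation of 0.4 and 30% drop-out. Re-sampling gives two-sided 0.05, 90% power, 31 evaluable and 45 recruited patients. Subgroup analyses gives three factors, each tested at p<0.10.

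**Assumptions not in the article.** The separate models are read at two-sided 0.05. The smaller subgroup holds 20%, 35% or 50% of patients for the three factors, independently of each other.

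**Step 1: the plan's own figure.** The SD of the within-patient difference is √(2 × 3² × (1 − 0.4)) = √10.8 = 3.286. A two-sided paired t test at 0.05 for 2 days has 89.6% power with 30 patients and 90.6% with 31. Then 31 / 0.7 = 44.3, rounded up to 45. The stated sample size reproduces.

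**Step 2: chance of at least one interaction hit when none exists.**
- Independent tests: 1 − (1 − 0.10)³ = 1 − 0.729 = 27.1%.
- Positively correlated test statistics: about 26% at a correlation of 0.2, 24% at 0.5 and 18% at 0.8.
- Simulated within-patient differences with a period term give about 26–28% with 31 or 45 patients.

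**Step 3: how large a difference must be to pass the gate.** With 31 patients split 16/15, the standard error of the interaction is 3.286 × √(1/16 + 1/15) = 1.18 days. The 0.10 critical value on 28 degrees of freedom is about 1.70, so the observed difference must exceed about 1.70 × 1.18 = 2.0 days. With a 6/25 split the standard error is 3.286 × √(1/6 + 1/25) = 1.49 days and the threshold is about 2.5 days. An interaction that triggers the separate models is therefore at least as large as the whole planned effect of 2 days, even when the true interaction is zero.

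**Step 4: what the separate models can show.** With the same SD and two-sided 0.05, power for a true 2-day effect is about 23% in a cell of 6 patients (20% of 31) and about 45% in a cell of 11 (35% of 31). The full model has six fixed effects including the intercept. In a cell of 6 patients observed in both periods it would be fitted to 12 observations, unless the comparison by Akaike's criterion removes the baseline terms.

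**Step 5: the whole rule, simulated.** Each trial tests the three interactions at 0.10 and, on a hit, fits the separate subgroup models at 0.05.

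| Scenario | At least one hit | One subgroup significant, complement not |
|---|---|---|
| 31 patients, uniform 2-day benefit | about 27–28% | about 21–22% |
| 45 patients, uniform 2-day benefit | about 26–28% | about 17–19% |

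The ranges cover repeated runs, including one set with 30% in place of 35% for the second factor. The simulation uses within-patient differences with a period term and omits the baseline covariates, so it approximates the planned mixed model.

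**The case against.** The plan follows good practice in several respects. The factors are few and named in advance, an interaction test comes before any subgroup model, and the article itself uses the cautious word trend for p<0.10. Detailed methodology is left to a statistical analysis plan that is not shown. All of this stands, and it is why the point is minor.

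Three stronger readings are tempting, and the article does not support them.

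- **The missing multiplicity rule or exploratory label is itself an error.** The article does attach that label elsewhere ("The secondary (exploratory) objectives are to assess the therapeutic efficacy") and not to the subgroups. But both matters are commonly settled in the analysis plan, so their absence here shows nothing.
- **A subgroup result could replace a negative primary test, so the trial's false-positive rate is inflated.** The Hypothesis section states one null hypothesis, on the overall comparison. The sample size serves that comparison alone, and Sensitivity analysis treats the main analysis as distinct from the subgroup analyses. No subgroup success criterion is written. A combined error rate over the primary and subgroup tests would describe a claim that the protocol does not make.
- **The Discussion already plans a subgroup claim**, because it mentions "moderately to strongly affected migraine patients, or at least a subgroup thereof". That sentence is conditional on proven efficacy, is speculative and does not refer to these tests.

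The figures also have limits. The 0.05 level for the separate models is carried over from the sample size section. The splits are assumed. The ITT set keeps some patients who drop out, so cells may be larger than those based on 31 completers. The 27% is the chance of an interaction signal, not of a false efficacy finding.

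The reading of p<0.10 and the gate to separate models remain. They are written in the protocol, and a later analysis plan would have to depart from them to avoid the problem.

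**Conclusion.** The point holds as a cheap improvement of minor severity. The written reading of p<0.10 overstates the evidence. With no true interaction, at least one of the three tests meets it in about 27% of trials under independence, and in about 18–26% under positive correlation.

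The gated separate models give selected and imprecise effects. Under the assumed 0.05 level and splits of 20%, 35% and 50% among 31 to 45 patients, a uniform 2-day benefit would appear as a benefit in one subgroup only in about one trial in five. That last figure depends on the assumptions; the first depends only on the stated threshold, the number of tests and their correlation.

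The primary test and its type I error are untouched.

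**What to change.** Change the Subgroup analyses section as follows.

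- Delete the p<0.10 gate and the separate models.
- For all three pre-specified subgroups, whatever the p-value, report the subgroup × treatment estimate with its 95% confidence interval. Report the subgroup-specific treatment effects as contrasts from the same joint model, also with intervals. If the treatment × baseline term is kept, state the baseline value at which the contrasts are taken.
- Replace the statement that p<0.10 indicates a difference with one that a low interaction p-value generates a hypothesis and supports no efficacy claim for a subgroup.

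This needs a few lines of text and no new data. The cost is a little more reporting, and a subgroup result can no longer be presented as evidence of efficacy in that subgroup.
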